**Plan of Investigation**

*Study Design*

The proposed study is a randomized, prospective, placebo-controlled, single-blind trial of electroacupuncture for residual insomnia associated with MDD. The study design aims to differentiate three plausible mechanisms for sleep improvement in patients with insomnia symptoms: (1) needling at specific sites based on traditional Chinese medicine (TCM) theory; (2) characteristic and incidental elements of acupuncture treatment, e.g. credibility of intervention, patient expectations;13 and (3) underlying fluctuations in the disorder, regression to the mean, or non-specific improvement associated with participating in a clinical trial.

Eligible patients will be randomized in a ratio of 1:1:1 to: (1) traditional electroacupuncture; (2) placebo acupuncture using Streitberger needle; and (3) waiting list control group. Active or placebo acupuncture treatment will be given 3 sessions per week for 3 weeks. Patients in the waiting list control group will not receive any treatment for a period of 8 weeks after randomization. After that time, they will receive the same treatment as in the traditional electroacupuncture group. The subjects’ sleep and residual symptoms will be assessed at baseline, after completing 2 weeks of acupuncture treatment, and at 1-week, 5-week and 13-week posttreatment.

*Subjects*

Outpatients, aged from 18 to 65 years, with a previous DSM-IV MDD and a chief complaint of insomnia will be invited to participate in this study. Written informed consent would be obtained prior to study procedure. Subjects would be excluded if they: (1) have a Hamilton Depression Rating Scale scores above 18; (2) have sleep apnea or periodic limbs movement disorder detected by overnight polysomnography; (3) have suicidal risk; (4) have previous history of schizophrenia, other psychotic disorders, and bipolar disorder; (5) are pregnant, breast-feeding, or woman of childbearing potential not using adequate contraception; (6) have infection or abscess close to the site of selected acupoints and in the investigator’s opinion inclusion is unsafe; and (7) are taking Chinese herbal medicine or over-the-counter drugs which are intending for insomnia.

The number of subjects to be recruited in each treatment group would be 30.

*Treatment Protocol*

Traditional Acupuncture

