SDI is a 3-item self-rating scale that assesses the subjects’ functioning regarding work/study, social life and family.

Objective assessment

Actigraph

Actigraph is a watch-like device used to estimate sleep-wake schedules by measurement of activity. The subjects are asked to wear the actigraph on the dominant wrists prior to light off for 3 consecutive nights. Subjects will be told to have usual bedtime when they are measured by actigraph.

Assessment for safety

Reason for withdrawal

When a subject withdraws before completing the study, the reason for withdrawal will be recorded.

Adverse events

Adverse events will be assessed at each visit. The researcher will ask using open-ended questions whether the subjects experience any adverse events during the assessment visit.

Assessment for credibility

Credibility of treatment rating scale (modified by C Vincent) will be used to assess the credibility of the treatments.17 The 4-item scale is specially designed to assess the credibility of acupuncture.

*Data Analysis*

Sample size estimation

Insomnia Severity Index (ISI) is selected as the primary outcome measure. The sample size estimation is based on our pilot study. We found that the SD of ISI score in the treatment and control group was 4.7 and 3.6, respectively, while the baseline and endpoint ISI score correlation coefficient was roughly 0.5. Vickers and Altman proposed that analysis of covariance (ANCOVA) was the preferred approach to analyse controlled trials with baseline and follow up measurements.18 We estimate the sample size requirement per treatment group using:

(1- ρ2)

An adjustment factor (1- ρ2) is used to determine the sample size in each group;19 and ρ is the baseline and endpoint measure correlation coefficient.

Let type I error a = 0.05; type II error β = 0.20; and power (1-β) = 80%. The SD δ1= 4.7, δ2 = 3.6 and ρ = 0.5. A clinically significant treatment effect is taken as a 3 ISI point between-group difference (Δ = 3). Therefore, a sample size of 23 is needed in each group. We estimate a 20% attrition rate; hence a sample size of around 30 in each group (90 in total) is planned for this study.

Data Management and Analysis

All data are double-entered and checked for consistency prior to analysis.

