Baseline differences between the electroacupuncture, minimal and placebo acupuncture groups would be examined using unpaired t-test or χ2 test. The last observation carried forward method would be used to handle missing data. The outcome measures during acupuncture treatment and at posttreatment would be compared with that at baseline using paired t-test. A 2 × 3 (time × group) ANCOVA with baseline measure as a covariate would be used to investigate differences between the electroacupuncture, minimal and placebo acupuncture groups. Standardized effect size would be computed by dividing the difference in means by the pooled standard deviation to estimate treatment impact. The clinical significance of the interventions would be estimated by the proportion of participants who reached sleep-diary SOL or WASO of 30 minutes or less and SE of at least 85%, and χ2 or Fisher exact test would be used to test for group differences.

Safety analyses

Subjects who receive at least 1 acupuncture treatment will be included for safety analyses. Adverse events will be coded using the WHO Adverse Reaction Terminology Dictionary. Special attention will be given to those subjects who have discontinued treatment due to an adverse event or who experience a severe or serious adverse event.

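### The safety set requires at least one acupuncture treatment, which does not suit a delayed-treatment arm: it excludes waiting-list subjects who leave before crossover and leaves the untreated comparison undefined

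*Protocol*

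**What the plan says.** The Protocol's Safety analyses paragraph gives one rule for entry to the safety population: "Subjects who receive at least 1 acupuncture treatment will be included for safety analyses". The rule works at the level of the subject. It names no period and no arm.

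Study Design sets out the allocation: "Eligible patients will be randomized in a ratio of 1:1:1 to: (1) traditional electroacupuncture; (2) placebo acupuncture using Streitberger needle; and (3) waiting list control". For the first two arms, "Active or placebo acupuncture treatment will be given 3 sessions per week for 3 weeks", so placebo sessions count as acupuncture treatment in the Protocol's own terms. For the third, "Patients in the waiting list control group will not receive any treatment for a period of 8 weeks after randomization". The crossover is then described as follows: "After that time, they will receive the same treatment as in the traditional electroacupuncture group".

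On collection, the Adverse events paragraph says "Adverse events will be assessed at each visit". Table 1 marks adverse event monitoring at every visit and has no separate schedule for the waiting list.

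Safety is named alongside efficacy in both the Objective and the Aims.

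**The concern.** Requiring at least one treatment is natural when every arm starts treatment at about the same time. Here the three arms enter the set on different terms. Electroacupuncture and placebo subjects qualify at their first session. Waiting-list subjects qualify only after staying for 8 weeks, during which they can have adverse events and are asked about them.

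Two consequences follow.

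- **Exclusion.** A waiting-list subject who leaves before crossover is not in the set, and neither are that subject's events. The same paragraph promises particular attention to severe or serious events, yet such an event in this subject would lie outside the population being analysed.
- **No separation of periods.** A subject who crosses over is in the set as one unit, with an untreated stretch followed by an electroacupuncture stretch. No single label for the whole subject fits both.

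At stake is the only untreated reference for adverse events. Subjects stay on antidepressants and may take sedatives, hypnotics or anxiolytics (Concomitant Therapy), and events are elicited by open-ended questions, so some background complaints can be expected in every arm. If leaving early is related to adverse events, the untreated rate seen among those who stayed will be too low.

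**Working it through.** **Group size.** The Protocol states no safety figure to reproduce. Its group size is used below, so that is checked first, with the inputs under Sample size estimation: SDs 4.7 and 3.6, correlation 0.5, difference 3, alpha 0.05 (taken as two-sided), power 80%.

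n = (1.960 + 0.842)² × (4.7² + 3.6²) / 3² × (1 − 0.5²) = 22.93, rounded up to 23. This agrees with the stated 23. Allowing for 20% attrition, 23 / 0.8 = 28.75, or 29, which fits the planned figure of around 30.

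**Inputs for the safety count.**

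- Waiting-list size: 30 (Subjects: "The number of subjects to be recruited in each treatment group would be 30"). The synopsis total of 96 would imply 96 / 3 = 32.
- Untreated period: 8 weeks, or 56 days (Study Design).
- Attrition: 20% (Sample size estimation). The Protocol does not say how much falls before crossover, so the share is assumed to lie anywhere from 0% to 100%.

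**Subjects excluded by the rule, and the untreated time that goes with them.**

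| Share of attrition before crossover (assumed) | Excluded, of 30 | Planned untreated patient-weeks excluded | Crossed over | Untreated patient-weeks brought in by crossed-over subjects |
| --- | --- | --- | --- | --- |
| 0% | 0 | 0 | 30 | 30 × 8 = 240 |
| 50% | 30 × 0.2 × 0.5 = 3 | 3 × 8 = 24 | 27 | 27 × 8 = 216 |
| 100% | 30 × 0.2 = 6 | 6 × 8 = 48 | 24 | 24 × 8 = 192 |

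The excluded patient-weeks are upper limits, because a subject who leaves before week 8 is observed for less than 8 weeks. With 32 per group the worst case is 32 × 0.2 = 6.4 subjects and 6.4 × 8 = 51.2 patient-weeks, which is essentially the same.

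**Time split for a crossed-over subject.** If followed to the D113 visit, 56 / 113 = 50% of that subject's time is untreated.

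**Visits set against the switch.** If Table 1 applies to the waiting list, the D15–D21 and D29 visits fall in the untreated period, D57 (± 4 days) falls at about the switch, and D113 falls after it. Up to about D57 all three arms share the same visits, so events can be compared on equal terms. After that no visit is scheduled until D113. Electroacupuncture given after crossover would therefore be watched less closely than in the arm randomised to it, which has visits at D15–D21, D29 and D57.

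**The case against.** The case for leaving the rule alone has real weight.

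- **The rule is conventional, and the main comparison is sound.** The aim is the safety of electroacupuncture. Placebo subjects are in the set, with the same number and duration of sessions, and supply a concurrent background rate. This stands in full.
- **The waiting list was included for another purpose.** Study Design gives its role as allowing for "underlying fluctuations in the disorder, regression to the mean, or non-specific improvement associated with participating in a clinical trial", and says so about sleep improvement. That is correct. The same reasoning carries over to adverse events, but the Protocol does not make that claim.
- **Assigning events to periods is normally left to the SAP, which is not shown.** This also stands, and silence on attribution alone would not be a finding. The membership rule is not silence, however. An SAP could add period labels, but it could not bring in never-treated subjects without departing from the Protocol.
- **The data are still collected.** Events could largely be sorted by visit afterwards, so this is a defect of analysis and reporting, not of collection.

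Three stronger readings are tempting, and the Protocol does not support them.

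- A reader might infer that untreated and post-crossover events will be pooled. The text prescribes no pooling and no grouping, and classifying events by treatment at onset remains open.
- A reader might infer that all 30 × 8 = 240 untreated patient-weeks are lost or mixed. Exclusion is certain only for subjects who never cross over. For any one subject the two harms are alternatives: the untreated events are either left out or carried in unlabelled.
- A reader might credit a change of rule with raising the electroacupuncture-exposed number from about 30 to about 60, lowering the one-sided 95% upper bound for an unseen event from 1 − 0.05^(1/30) = 9.5% to 1 − 0.05^(1/60) = 4.9%. The present rule already admits every waiting-list subject who receives electroacupuncture, so this is not a gain from the fix. It also assumes that all of them cross over.

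**Conclusion.** The point holds in a limited form. The safety set does not suit a trial with a delayed-treatment arm. Between 0 and about 6 of 30 waiting-list subjects, with at most 48 patient-weeks, are excluded by rule. The upper end rests on the assumption that all of the Protocol's 20% attrition falls before crossover. The numbers are small, but the exclusion depends on leaving the trial, and it removes any serious events these subjects had.

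The other 24 to 30 enter with about 8 untreated weeks each that the rule does not set apart from their electroacupuncture period. The concurrent untreated comparison is thus selected on retention and left undefined.

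Electroacupuncture versus placebo is unaffected, as are the efficacy analysis and the sample size. The statements about visit timing assume that Table 1 applies to the waiting list, which the Protocol does not say.

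**What to change.** Revise the Safety analyses paragraph so that:

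1. the safety analysis includes all randomised subjects;
2. adverse events up to week 8, before crossover, are reported by arm, with the waiting list shown as untreated and including those who never cross over;
3. waiting-list events after the start of electroacupuncture are reported separately. If they are also pooled with the electroacupuncture arm for exposure-based rates, the report should note the sparser visits after D57, should Table 1 apply to that arm.

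The present set of subjects with at least one treatment can be kept as an additional, exposed population.

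The cost is revised wording, one more column in the adverse-event tables, and an onset date or visit for each event. An onset date is preferable around D57, where the visit window straddles the switch. No additional subjects or visits are needed, and no sample-size figure changes.
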